**Fig. 1 Fig1:**
[figure not shown]
Schedule of enrollment, interventions, and assessments in the study

### Questionnaires

A literacy assessment instrument (BOHLAT-P), validated for Brazilian Portuguese language, will be used to evaluate the mothers’ oral health knowledge, textual understanding, and numerical skills [33, 34]. The first part evaluates basic knowledge in oral health, from images illustrating normal deciduous dentition and dental caries. The second part measures the numerical abilities of the individual, being represented by four groups of questions. The first refers to an appointment card already completed, questioning the date and time of the next appointment, with the contact number of the clinic. The second group of questions is related to a drug prescription, in which the respondent is asked about the date of validity of the medication presented, adequate dose interval, and duration of treatment. The third group of questions revolves around post-surgical instructions, which cover aspects such as warm diet introduction period, oral hygiene, and conduct facing complications. The fourth group of questions has as its central axis a dentifrice label, addressing points such as brushing frequency and ideal dentifrice amount. The last part of the instrument evaluates textual comprehension and vocabulary. It consists of a dialogue between the dentist and the child’s mother addressing the exchange of dentitions with blank passages to be completed from the answer options presented. Lastly, there is a brushing guide whose instructions need to be sorted correctly.

A self-report questionnaire containing a series of questions ordered in the form of questions, addressing issues such as identification, socioeconomic status, maternal and paternal education, occupation of the mother and person with higher family income, health conditions, access to health services, and oral health care measures will be applied before interventions [35, 36].

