Dental studies have achieved good results using an oral health education tool to inform and motivate adolescents [22, 23]. A digital medium with widespread use in Brazil is WhatsApp Messenger, which is an application that allows rapid interaction through texts, images, voice and video calls [24]. Consequently, this application may be an effective social media tool for disseminating health education [25]. In this context, a 2016 survey conducted in Brazil showed that 76% of users who searched the Internet made continuous use of WhatsApp, and this percentage is one of the highest worldwide, second only to South Africa [26]. However, the efficacy of using WhatsApp to promote oral health education for mothers and children has not yet been elucidated in the literature.

The objective of this parallel, double-blind, and randomized clinical trial is to compare the influence of conventional education promoting oral health, versus that of conventional education plus the WhatsApp digital platform, in controlling dental biofilm and caries in mother-child pairs. Mothers and their children (age 6–12 years) will be evaluated through a self-administered questionnaire on oral hygiene habits, and through the Oral Health Literacy Assessment Task for Paediatric Dentistry (BOHLAT-P). In addition, clinical parameters of the mother-child pairs (including the visible plaque index [VPI], gingival bleeding index [GBI], number of decayed, missing, and filled deciduous teeth [dmft], and the numbers of decayed, missing, and filled permanent teeth [DMFT modified by the inclusion of active non-cavitated carious lesions]) will be considered in the assessment. We hypothesized that mother-child pairs randomized to the experimental group would exhibit greater improvements in oral hygiene behavior and health outcomes when compared with the control group during follow-up assessments at 1, 6, and 12 months.

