### Interventions

The following study groups will be created in parallel to evaluate the proposed intervention. (1) Control group: Both mothers and children will undergo clinical examination, prophylaxis, topical fluoride application, and oral hygiene guidance on a single dental office visit. The pairs will receive an oral hygiene in-person orientation session that will take about 30 min regarding to oral health, gingival health, sugar intake, fluoride importance in prevention of dental caries, and oral hygiene habits, complemented with illustrative resources.

(2) Experimental group: Both mothers and children will receive clinical examinations, prophylaxis, topical fluoride application, and oral hygiene guidance on a dental office visit. Additionally, the digital platform WhatsApp Messenger (Mountain View, California) will be used to provide educational videos to the mother-child pairs, twice per week (Tuesday and Thursday) at 7 PM over a period of 4 weeks. A WhatsApp video presenting a story on oral health, along with a reminder to perform their oral hygiene routine (toothbrushing and flossing) will be sent to the mother-child pairs in the experimental group. Topics including oral hygiene, dental biofilms, white spot lesions, dental caries, and the importance of dental appointments will be covered. Videos were validated by educators and a group mother-child pairs who evaluated the quality of the animated videos and understanding of the topics covered according to Marinho et al. [27].

At the end of 4 weeks (T1), 6 months (T2), and 12 months (T3), the mother-child pairs will undergo follow-up clinical evaluations at FORP/USP. If needed, dental treatment will be performed by a research team at the same institution.

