### Outcome measurements

Measurements will be taken at baseline, post-intervention (i.e., 30 days after completion of the intervention), and at the 6-month and 12-month follow-up points. All follow-up assessments will be conducted by a researcher blinded to the group allocation of the participants.

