### Measurement of secondary outcomes

The secondary outcome is defined as the participant responses to the questionnaire on socioeconomic data, oral hygiene, visits to the dentist, and acceptability of the animation by the pairs mother-child. At the end of T3, the mothers of the experimental group will be asked if the videos were watched at the moment they were sent or if they was watched in other times after the intervention. Question will include how often the videos were watched, which videos they and their children liked the most, and what subject was easier or more difficult to understand and suggestions for improvement. Quality of life will be evaluated using the BOHLAT-P questionnaire [33]. This questionnaire contains 49 questions and is divided into three domains: oral health knowledge, textual understanding, and numerical skills [34]. The mother will answer the BOHLAT-P questionnaire alone, and the researchers will provide help if requested.

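### The hygiene questionnaire is scheduled before the interventions although its responses are a secondary outcome, and video viewing is first asked about 11 months after the last video

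*Protocol article*

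**What the plan says.** All references are to the protocol article.

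- **Questionnaires** gives the only timing attached to the self-report instrument. Its items, including "health conditions, access to health services, and oral health care measures will be applied before interventions". No later administration is mentioned.
- **Measurement of secondary outcomes** makes the answers an endpoint: "The secondary outcome is defined as the participant responses to the questionnaire on socioeconomic data, oral hygiene, visits to the dentist". Acceptability of the animation belongs to the same outcome.
- **Background** states the hypothesis that pairs in the experimental group "would exhibit greater improvements in oral hygiene behavior and health outcomes when compared with the control group", at 1, 6 and 12 months. It also says that hygiene habits are assessed by a self-administered questionnaire.
- **Outcome measurements** sets a general schedule without naming instruments: "Measurements will be taken at baseline, post-intervention (i.e., 30 days after completion of the intervention), and at the 6-month and 12-month follow-up points".
- **Baseline data** lists socioeconomic data as collected at baseline.
- **Interventions** has the videos sent "twice per week (Tuesday and Thursday) at 7 PM over a period of 4 weeks".
- **Measurement of secondary outcomes** also fixes the viewing questions: "At the end of T3, the mothers of the experimental group will be asked if the videos were watched at the moment they were sent". How often the videos were watched, which were preferred and what was hard to understand are asked with them.

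**The concern.** An answer given before the interventions can describe the arms at entry and nothing more. It cannot show change, and any difference between randomised arms at that point is chance. If hygiene habits and dental visits are endpoints, and the hypothesis concerns improvement in behaviour, the instrument has to be given again after the intervention, in both arms. The one section that fixes its timing does not provide for that.

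The viewing questions raise a different problem. They are the only stated record of whether the experimental arm received the intervention in any real sense. If the trial shows no difference, the reader will want to know whether the videos failed or were not watched. Asked nearly a year later, a mother's account of whether she watched each video when it was sent, and how often, is weak evidence. A mother lost before T3 gives none.

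**Working it through.** **Part 1: questionnaire timing.** No arithmetic applies, so the sections are set side by side.

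| Section | What it implies for self-reported hygiene and dental visits |
|---|---|
| Background | Needed after the intervention, at 1, 6 and 12 months, in both arms |
| Questionnaires | Given before the interventions; no repeat stated |
| Outcome measurements | Measurements at baseline and three follow-ups; instruments not named |
| Measurement of secondary outcomes | Responses are an endpoint; acceptability, in the same outcome, can be answered only after the videos are sent |
| Baseline data | Socioeconomic items belong at baseline |

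Three other places point towards follow-up visits that are clinical only, though none settles it. The Abstract ties its before-and-after assessment to the plaque, bleeding and caries indices, and mentions the questionnaires in a separate sentence with no timing. The Interventions section describes T1, T2 and T3 as clinical evaluations. The Statistical analyses section assigns a test over time within groups only to plaque and bleeding.

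The Questionnaires section is specific to the instrument and the Outcome measurements section is not. A team that follows the specific instruction collects no self-reported behaviour after the intervention. A team that follows the general one collects it three times. The text does not say which is meant.

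**Part 2: recall interval for viewing.**

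Inputs:
- Two videos a week for 4 weeks (Interventions): 2 × 4 = 8 videos.
- The last video falls in the fourth week, so between day 22 and day 28.
- Visit times, from Interventions: "At the end of 4 weeks (T1), 6 months (T2), and 12 months (T3), the mother-child pairs will undergo follow-up clinical evaluations".
- One month is taken as 30.4375 days, so 12 months = 365.25 days.

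Gap from last video to T3, counting T3 from baseline = (365.25 − day of last video) / 30.4375:
- last video on day 22: 343.25 / 30.4375 = 11.3 months
- last video on day 28: 337.25 / 30.4375 = 11.1 months

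If T3 is instead counted from the end of the 4 weeks, 28 days are added:
- last video on day 22: 371.25 / 30.4375 = 12.2 months
- last video on day 28: 365.25 / 30.4375 = 12.0 months

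Gap if the same questions were asked at T1. The article times this visit in two ways, so both are shown:
- T1 at the end of 4 weeks (Interventions): 28 − 28 = 0 to 28 − 22 = 6 days
- T1 at 30 days after completion (Outcome measurements), which is day 58: 58 − 28 = 30 to 58 − 22 = 36 days

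On either definition of T1, recall falls from about 11 months or more to at most about five weeks. No sample size or power figure is affected.

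**The case against.** A reader might infer that behaviour is measured at none of the three follow-up visits, so that the behavioural hypothesis cannot be tested. The documents do not support that. The Questionnaires section does not say that the instrument is given only once. The general schedule in Outcome measurements stands at the head of the outcome sections and can be read as covering the secondary outcomes. Acceptability of the animation must be collected after the videos, so part of the questionnaire outcome is certainly post-intervention. Fig. 1, captioned as the assessment schedule, is not available here and may show a repeat. What stands is a conflict in the text, not proof that follow-up administration is excluded.

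It is also fair to say that hygiene does not go unmeasured. VPI and GBI are primary outcomes compared with control throughout follow-up, and the examination section classes hygiene by them. They measure the result of behaviour rather than reported behaviour, so the objection limits the harm to self-reported secondary data without removing it.

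On viewing, a reader might infer that asking at T3 yields nothing useful. That too goes further than the text. Whether videos were watched again later needs a late visit, and preferences and suggestions can still be given then. No named test uses viewing. The weakness is confined to items about what happened during the 4 weeks. An earlier form carries a risk of its own: it reveals allocation while the blinded examiner still has T2 and T3 to assess.

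It may further be suspected that control families saw forwarded videos. The article says only that videos are sent individually to experimental participants, and nothing in it bears on forwarding, so this is not part of the point.

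Finally, listing socioeconomic data as an outcome may be loose wording, since Baseline data already places them correctly. That is a reason to tidy it, with no analytic harm claimed.

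**Conclusion.** The point holds in two limited parts.

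1. The stated timing of the self-report questionnaire conflicts with its role as a secondary outcome, with the behavioural hypothesis at 1, 6 and 12 months, and with the general measurement schedule. If the Questionnaires section governs, self-reported hygiene and dental visits cannot be compared between arms after the intervention. The primary clinical indices are unaffected.
2. Viewing during the 4-week programme is first asked about 11 months after the last video (11.1 to 11.3 months from a baseline count, 12.0 to 12.2 months if T3 runs from the end of the programme). Adherence data are exposed to long recall and are missing for mothers who leave before T3.

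This assumes that the items on care measures and access to services in the Questionnaires section are those meant by oral hygiene and dental visits in the outcome definition. That is plausible, but the article does not say so. It also assumes that Fig. 1 does not already resolve the timing. If it does, the Questionnaires text still needs correcting to match. The change is worth making because behaviour not recorded at a visit cannot be properly recovered afterwards.

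**What to change.** - **Questionnaires:** state that the hygiene and dental-visit items are given at baseline and repeated unchanged at T1, T2 and T3 in both arms. Say that change from baseline will be compared between arms.
- **Measurement of secondary outcomes:** remove socioeconomic items from the outcome and leave them under Baseline data.
- **Viewing and acceptability:** add these questions at T1 for the experimental arm. Keep re-watching and overall feedback at T3.
- **Blinding:** have mothers complete the viewing form themselves, and have it handled by the researcher who sends the videos and already knows the allocation, never by the blinded examiner.
- **Pairs already past T1:** start the repeated items at their next visit. The article gives recruitment as running from January to an anticipated end in December 2022, so some pairs may be affected.

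The cost is a few extra minutes of form-filling at visits already scheduled, and a small risk of unblinding if the viewing form is not kept from the examiner. No sample size figure, examination or treatment changes.

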### Outcome measurements

Measurements will be taken at baseline, post-intervention (i.e., 30 days after completion of the intervention), and at the 6-month and 12-month follow-up points. All follow-up assessments will be conducted by a researcher blinded to the group allocation of the participants.

### Baseline data

Sociodemographic and socioeconomic data will be collected at baseline, including the participant’s age, gender, skin color, household income, and educational literacy level.

### Measurement of primary outcomes

The primary outcome is defined as the effectiveness of educational videos via WhatsApp Messenger for controlling dental biofilm and dental caries in mother-child pairs. This outcome will be achieved by evaluating the VPI, GBI, and dmft indexes for deciduous teeth, and the DMFT for permanent dentition. Dental caries will be evaluated using the Nyvad Criteria to assess severity and activity of carious lesions. These results will be compared with those of the control group throughout the follow-up.

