### Inclusion criteria

All mothers have to be at least 18 years old

Children (6–12 years old) of both sexes

Participants (mother-child pairs) with good general health (reported by the mother)

Mothers using WhatsApp Messenger on their smartphones

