Theoretical training took place for an examiner ([name]) along with the reference standard examiner ([name]) through expository classes regarding the following indexes: VPI; GBI; decayed, missing, and filled permanent teeth (DMFT); and decayed, missing, and filled primary teeth (dmft) and Nyvad criteria to assess active non-cavitated carious lesions. Oral examination of the mother-child pairs will be performed by a trained and calibrated operator ([name]) and assisted by a trained annotator ([name]). The examinations will be performed with the mother-child pairs seated in front of the examiner. The dentist will be used individual protection equipment, a sterilized flat oral mirror (Golgran, São Caetano do Sul, São Paulo, Brazil), and a sterilized periodontal probe (WHO-621, Trinity®, Campo Mourão, PA, Brazil). The visible plaque index (VPI) will be used to evaluate the mesial, distal, vestibular, and lingual surfaces of the incisors and first upper and lower molars according to the criteria set by Ainamo and Bay [28]. Evaluations will be performed by direct visualization of the vestibular and palatine/lingual surfaces. A flat oral mirror # 5 (Golgran, São Caetano do Sul, São Paulo, Brazil) will be used for the visual examination. The established scores for the VPI are (1) presence and (0) absence. For the gingival bleeding index (GBI), a periodontal probe (WHO-621, Trinity®, Campo Mourão, PA, Brazil) will be used to evaluate the subgingival surfaces 1 mm into the sulcular epithelium. The bleeding on probing index will also be recorded as (1) presence of bleeding and (0) absence of bleeding. Oral hygiene will be considered unsatisfactory if the percentage of visible biofilm is greater than 15% and/or gingivitis is present, as indicated by bleeding at more than 15% of the evaluated sites [25, 28].

After brushing, a clinical oral examination will be performed to verify the participants’ oral health condition, and the data will be recorded using the dmft and DMFT index for deciduous and permanent teeth, respectively [29, 30]. Dental caries will be evaluated using the Nyvad Criteria to assess severity and activity of carious lesions, including lesions of rough and opaque white spots [31]. The initial evaluation aims to verify the inclusion criteria for the study participants. Subsequent evaluations will aim to assess the effectiveness of the interventions for improving the oral hygiene of the mother-child pairs.

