### Statistical analyses

Data will be analyzed using the GraphPad Prism 8.0 software (GraphPad Software Inc., San Diego, CA, USA). Descriptive analyses, including percentages, means, and standard deviations, will be reported. Answers to the BOHLAP-T questionnaire will be dichotomized into correct and wrong answers. Each correct answer will receive a score of 1, and each wrong answer will receive a score of 0. The maximum and minimum scores are 49 and 0, respectively. The chi-square test will be used to analyze categorical variables, the Mann-Whitney test will be used to compare the inter-group differences, and Friedman test will be used to calculate intra-group differences in relation to VP and GBI. The following tests will be used to analyze the experience of caries: *t* of “Student” and of chi-square. The significance level will be set at 5%.

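### The primary outcome is a bundle of four or five indices, in mother and child, at three visits, with no lead endpoint and no rule for what counts as success

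*Protocol article*

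**What the plan says.** Under Measurement of primary outcomes the protocol article gives a concept and not a variable: "The primary outcome is defined as the effectiveness of educational videos via WhatsApp Messenger for controlling dental biofilm and dental caries in mother-child pairs". It then lists how the concept is measured: "This outcome will be achieved by evaluating the VPI, GBI, and dmft indexes for deciduous teeth, and the DMFT for permanent dentition". The next sentence adds: "Dental caries will be evaluated using the Nyvad Criteria to assess severity and activity of carious lesions". On timing it says only: "These results will be compared with those of the control group throughout the follow-up". The Background places follow-up at 1, 6 and 12 months.

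The Background and the Methods part of the Abstract treat the lesion assessment differently, describing a "DMFT modified by the inclusion of active non-cavitated carious lesions". On that reading Nyvad feeds the caries index and is not an endpoint of its own.

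Both members of the pair are measured: "Oral examination of the mother-child pairs will be performed by a trained and calibrated operator" (Interventions).

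Statistical analyses assigns Mann-Whitney to between-group differences in plaque and bleeding, and Student's t and chi-square to caries experience. Its only statement on error control is "The significance level will be set at 5" percent. Sample size and power calculation gives 44 pairs per group at alpha 5% and power 80%, based on a study of a game for delivering oral health knowledge. It names no index, effect size or standard deviation.

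**The concern.** A primary outcome has two jobs. It fixes which comparison decides the trial, and it is the comparison to which the 5% error rate and the sample size apply. Here neither job is done. The listed measures also behave differently: plaque and bleeding can change within weeks, whereas cumulative caries counts move slowly. A mixed picture is therefore plausible, for example mothers' bleeding better at 1 month and children's plaque no different at 12 months. The article offers no way to say whether such a trial succeeded. The authors could choose the index, the person and the visit after seeing the data and still be within the text. The sample size does not reveal the intended lead endpoint, because it is tied to none of the listed indices.

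**Working it through.** **1. The plan's own figure.** The 44 pairs per group cannot be reproduced, because no effect or standard deviation is given. It can only be solved backwards. For two means, n per group = 2(z₀.₉₇₅ + z₀.₈₀)²/d², so d = (1.960 + 0.842) × √(2/44) = 0.597 two-sided. One-sided it is 0.530. Neither value points to a particular index.

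**2. Number of between-arm comparisons.** Mothers are adults ("All mothers have to be at least 18 years old"), so the deciduous index is counted for children only.

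| Reading of Nyvad | Child | Mother | Per visit | Three visits |
|---|---|---|---|---|
| Part of modified DMFT | VPI, GBI, dmft, DMFT = 4 | VPI, GBI, DMFT = 3 | 7 | 21 |
| Separate measure | 5 | 4 | 9 | 27 |

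That every index is tested at every visit is an inference from the statement that comparison runs throughout follow-up.

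**3. Error if any one significant result counts.** This success rule is an assumption. With m independent tests at 5%, the chance of at least one false positive is 1 − 0.95^m:
- m = 21: 1 − 0.95²¹ = 0.659
- m = 27: 1 − 0.95²⁷ = 0.750

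Independence is the extreme case. The same mouths are scored repeatedly, the indices are related, and mother and child share a household. The documents give no correlations, so the next table assumes a common correlation ρ between normal test statistics, each tested two-sided at 5%.

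| Tests | ρ = 0 | ρ = 0.5 | ρ = 0.7 | ρ = 0.9 |
|---|---|---|---|---|
| 9 (one visit) | 37% | 27% | 20% | 12% |
| 21 | 66% | 43% | 30% | 16% |
| 27 | 75% | 48% | 33% | 17% |

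A more structured assumption gives a similar picture. With separate correlations between visits (0.5 to 0.9), indices (0.3 to 0.9) and pair members (0.3 to 0.9), the result is about 19% to 57% for 21 tests and 21% to 66% for 27.

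**4. If all comparisons must succeed.** The type I error stays at or below 5%, and the cost moves to power. With only two independent endpoints at 80% power each, joint power is 0.8 × 0.8 = 64%. It falls further with each added endpoint, though less steeply when endpoints are positively correlated.

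**5. If every comparison is kept as a route to success and alpha is split equally.** Using the back-solved d = 0.597 (itself an assumption) and alpha = 0.05/m:

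| m | Alpha per test | Pairs per group for 80% power | Power at 44 | Power at 50 |
|---|---|---|---|---|
| 9 | 0.00556 | 74 | 51% | 59% |
| 21 | 0.00238 | 85 | 41% | 48% |
| 27 | 0.00185 | 88 | 38% | 45% |

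The planned 50 pairs per group would not carry the whole bundle at 80% power for each test.

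**The case against.** The strongest reply has four parts.

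- **No any-one-wins rule is written.** A reader might infer that the trial does not deliver its stated 5%, full stop. The documents do not support that. The outcome is worded as control of biofilm *and* caries in pairs, which can also be read as needing both, and then the type I error is not inflated. This stands: the inflation is conditional on a rule that the article does not state.
- **The count can be overstated.** A reader might infer at least five indices. The sentence that lists them names four, and the modified-DMFT wording lets Nyvad be absorbed into caries. This also stands, so the supportable range is 21 to 27 comparisons. Likewise 75% is only the independence end of the range.
- **Multiplicity methods may sit in an analysis plan that is not shown.** That is fair for the adjustment procedure, so its absence here is not the point. It does not cover the choice of primary variable, person and visit. The article has a section for that choice and fills it with a bundle.
- **The documents do not rank child over mother, plaque over caries, or 12 months over 1 month.** Correct, and any single choice narrows the stated objective. This limits how prescriptive the remedy can be but does not remove the need for one.

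**Conclusion.** The point holds in this form: the primary outcome is fixed as a bundle of four or five indices in two people at three visits, under one 5% level, with no lead endpoint and no success rule. The defect that rests on no assumption is that mixed results have no predefined reading. The numerical consequence is conditional. Under an any-one-significant rule the false positive risk is about 16% to 75%, so even the low end (21 tests, ρ = 0.9) is about three times the nominal level. Under an all-must-succeed rule the error is controlled and power is lost. The correlations are assumed throughout. Because this decides what the trial may conclude, it must be corrected before any unblinded look at the data.

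**What to change.** Before any unblinded look, amend the protocol and the registry entry to do the following.

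1. Name one primary index, person and visit, with its test. One defensible example is the child's VPI at 12 months, compared between arms two-sided at 5%: biofilm is the first-named target and 12 months is the full follow-up. The documents do not dictate this choice, and another single endpoint would also cure the defect. Alternatively, keep more than one primary endpoint under an explicit co-primary rule (any or all) with its alpha.
2. Make the other indices, the other member of the pair and the other visits secondary, tested with Holm or in a fixed order.
3. Say whether Nyvad status is a separate endpoint or part of the modified DMFT.
4. State which endpoint the 44 pairs per group refers to. If it is not the one chosen, recompute the power for that endpoint.

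The cost is a short amendment and a power check, with no new data collection for items 1 to 3. Item 4 could matter more: recruitment had begun in January 2022, and power for any listed index cannot be checked from the article. The scientific price is that a positive result on a non-primary index, person or visit can no longer be presented as the main finding.
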